### Data collection

We will collect patients’ basic information, disease history, health information, digital X-ray result, TB laboratory test results for TB, and clinical diagnosis, as well as routine TB reporting data. All data will be entered into a data-reporting website designed for this project, accessible only by designated researchers via local intranet with a password. Individual data will be de-identified and stored for five years after the completion of the trial.

#### ACF activities.

During the ACF, we will collect information about TB symptoms, including chronic cough for more than 2 weeks, hemoptysis, blood sputum, fever, night sweats, chest pain or unexplained weight loss, and TB risk factors (close contact history of tuberculosis patients, diabetes, AIDS/HIV and dust exposure). We will also collect the number of permanent residents of the village at the time of ACF, and the number of high-risk populations.

#### Laboratory testing and clinical consultation.

The county hospitals will carry out laboratory testing according to the ‘TB Laboratory Testing Protocol’. Sputum smear test, GeneXpert test and sputum culture are carried out at the same time. Every five samples of sputum will be mixed for GeneXpert test to save costs. Mixed samples that are positive will be re-tested individually to confirm the positive case. Country hospitals will distribute the laboratory testing results to patients within 48 hours. All TB diagnoses will be recorded in the ‘Register of Newly Diagnosed Patients’ in the National TB Program Registry. Clinical diagnosis based on the clinical assessment will be performed by a group of senior doctors in county hospitals according to the National TB Classification Criteria (WS196–2017) and Diagnostic Criteria (WS288–2017) [19,20]. We will collect TB cases diagnosed and reported in the National TB Program in both intervention and control groups through the three years.

#### Determination of the primary and secondary outcomes.

We will combine the TB cases identified from the Year 3 prevalence survey and TB cases reported from the National TB Program to determine the numerators of our outcomes. The data collection approach in Year 3 for the outcome evaluation will be the same as the ACF activities conducted in the intervention group in Year 1. We will use the TB diagnosis algorithm as defined in our ACF to determine the bacteriologically confirmed and clinically confirmed cases. We will also collect the routinely reported TB cases through the National TB Program for Year 3. We will collect the information of all registered permanent residents who reside in the village at the time of Year 3 survey to determine the relevant denominators.

### Statistical analysis

The results of this project will be reported according to the ‘Consolidated Standards of Reporting Trials: Extension for Cluster Trials’ (CONSORT) guidelines [21]. We will report a detailed statistical analysis plan later. In the full research paper, we will present appropriate descriptive statistics for the two groups and all relevant baseline cluster and participant characteristics. We will aggregate information collected in Year 3 prevalence survey at the township level to calculate primary and secondary outcomes. In addition, using cluster-level methods of analysis, we can get a main set of estimates for our primary and secondary outcomes after the trial, acting as the primary evidence for determining the effectiveness of this trial. Appropriate summary statistics and their associated 95% confidence interval for all differences outcomes between the intervention group and the control group will be calculated. No interim analyses are involved in this project.

For the primary outcome and all secondary rate-based outcomes (aggregated to the township level), the statistical analysis will employ a beta-binomial regression model. The intervention effect will be expressed as an odds ratio with 95% confidence intervals. Secondary analyses will attempt to analyze the patient-level data adjusted for age, sex, and ethnicity using a mixed-effects logistic regression model including random effects for township and village (to reflect the sampling strategy). In the event of non-convergence of the two-level model, models where township is included as a fixed effect rather than random will be employed.

For continuous secondary outcomes we will employ a linear mixed-effect model with random effects for township and village. This model will also adjust for the following variables: age, sex, and ethnicity. In the event of non-convergence of the two-level model, models where township is included as a fixed effect rather than random will be employed. The intervention effect will be expressed as the adjusted mean difference with 95% confidence intervals.

We will conduct subgroup analyses by county to reflect if there is any different effect due to environmental factors in each county. If the secondary patient-level analyses can be successfully employed, a sub-group analysis by sex will be attempted.

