### Recruitment, randomization and blinding

There are 23 townships and 255 villages in Xincheng and Xiangzhou county of Laibin city [17]. We will implement the ACF activities at the township level to avoid contamination among villages because township hospitals manage village doctors. We seek to recruit all townships of the two counties. After recruitment, the study statistician will use a custom-written computer program to randomize all recruited townships, stratified by county, assigning them to the control and intervention group in an overall 1:1 ratio (12 intervention vs 11 control) [18]. Then township/village doctors and county hospital staff in the intervention group will be invited to receive training about specific interventions in this project. After randomization is done at the township level, the statistician will then randomly select 47 villages, stratified by county, from each group for the Year 3 prevalence survey. The selection of villages for prevalence survey will be sealed and blinded to providers and investigators until the Year 3 prevalence survey to prevent any provider-related bias. We will seek written informed consent from each participant before enrollment, as we need to collect their health information, bio-sample (sputum) and test result for research purpose.

Due to the nature of the intervention, neither single nor double blindness procedure of the allocation of groups is applicable. However, we will blind the data analysts who process the end-point data for outcome assessment.

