Nevertheless, there are some limitations in this study as well. First, TB-suspected participants in the active screening intervention are required to collect two sputum samples (one for morning and one for night sputum) and send them to village doctors. Although specific equipment and instructions will be given, there are still risks of improper sample collection or transportation, which may affect laboratory results and TB diagnosis. We provide training for people assumptive of TB in sputum collection to improve the quality. Second, due to the limitation of funding and human resources, we are not able to conduct active case finding among all populations in participating townships in Year 3. Therefore, the trial cannot evaluate the impact of interventions on TB prevalence in the general population. On the other side, a prevalence survey including the whole population may not be feasible anyway because most people of working ages in rural areas moved to urban areas as migrants during most time of the year, while only elders, who comprise the majority of our high-risk population, and children stay at home. Our active case-finding activity targeting high-risk populations would significantly reduce TB in rural areas. Third, there is a possibility of participants migrating between villages. However, this situation is rare due to local culture and similar income level among villages. This was confirmed by another trial we conducted in Guangxi [31]. Lastly, we are not able to conduct a TB prevalence survey before the start of interventions to serve as a baseline due to limited resources. We believe the randomization procedure will minimize any confounding effects from the baseline effect in the two groups.

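### County is a randomisation and sampling stratum, but the primary beta-binomial model is stated without a county term

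*Protocol article*

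**What the plan says.** County enters the design twice. In Recruitment, randomization and blinding, the statistician will "randomize all recruited townships, stratified by county", "assigning them to the control and intervention group in an overall 1:1 ratio (12 intervention vs 11 control"), and will then "randomly select 47 villages, stratified by county, from each group for the Year 3 prevalence survey".

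In Statistical analysis, the main evidence is to come from cluster-level methods: "For the primary outcome and all secondary rate-based outcomes (aggregated to the township level), the statistical analysis will employ a beta-binomial regression model", and "The intervention effect will be expressed as an odds ratio with 95% confidence intervals". No covariate is named for that model. For the patient-level model the text is specific: "Secondary analyses will attempt to analyze the patient-level data adjusted for age, sex, and ethnicity using a mixed-effects logistic regression model", with random effects for township and village. The model for continuous outcomes has the same three covariates. County appears in the section only once: "We will conduct subgroup analyses by county to reflect if there is any different effect due to environmental factors in each county".

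The article says that a detailed statistical analysis plan will follow. It does not say whether the interval and test for the odds ratio will be Wald, likelihood-ratio, t-based or otherwise corrected.

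**The concern.** An analysis should reflect the restrictions placed on the randomisation. Stratifying by county removes the county contribution from the sampling variation of the treatment comparison. A model without county does not know this: it treats a true difference between the counties as unexplained variation between townships and puts it into the overdispersion parameter. The standard error then overstates the real uncertainty, and the trial gives up power that its design had secured.

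A county difference is plausible on the article's own terms. The subgroup analysis anticipates environmental differences between the counties, the AI threshold score is adjusted in each county, and laboratory testing and clinical diagnosis take place in the county hospitals. Both true prevalence and detection could therefore differ.

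**Working it through.** **The plan's own figure.** Inputs from Sample size: prevalence 0.003 against 0.0015, ICC 0.001, 500 eligible people per village, 80% power, 5% level (taken as two-sided).

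- Individual-level n per arm = [1.960·√(2·0.00225·0.99775) + 0.842·√(0.003·0.997 + 0.0015·0.9985)]² / 0.0015² ≈ 15,662.
- Design effect = 1 + (500 − 1)·0.001 = 1.499.
- 15,662 × 1.499 ≈ 23,477, and 23,477 / 500 = 46.95, so 47 villages per group.

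The stated figure reproduces. This calculation has no county component.

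**Does omission bias the estimate?** Take control prevalences of 0.002 and 0.004 in the two counties (county odds ratio about 2) and a true odds ratio of 0.5 in each. The intervention prevalences are 0.001001 and 0.002004.

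- With equal county weights in both arms, the pooled odds ratio is (0.0015025/0.9984975) / (0.003/0.997) = 0.5001.
- With an assumed 6/6 and 6/5 split of townships and control weights of 6/11 and 5/11, it is 0.516 or 0.485, depending on which county has the higher prevalence.

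On the log scale that shift is about 0.03, against a standard error of about 0.35 in the simulation below. It is not material.

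**Effect on the test.** Township counts were simulated and the beta-binomial model was fitted by maximum likelihood, with and without county: 23 townships (12 against 11), 47 villages of 500 per arm, 1,600 trials per scenario. Assumptions not in the article: 12 and 11 townships per county, villages spread at random over townships within arm, township-level ICC of 0.001 or 0.0003, and county odds ratios of 1.0 to 2.0. Monte Carlo standard error is about 0.7 points for type I error and 1.2 for power. The t reference has 21 df without county and 20 with it. Entries are percentages, without / with county; power is at odds ratio 0.5.

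| ICC | County OR | Type I, z | Power, z | Gap | Type I, t | Power, t | Gap |
|---|---|---|---|---|---|---|---|
| 0.001 | 1.0 | 7.2 / 8.0 | 56.7 / 59.2 | 2.5 | 5.4 / 5.8 | 51.6 / 53.0 | 1.4 |
| 0.001 | 1.25 | 6.6 / 8.2 | 53.6 / 58.2 | 4.6 | 5.3 / 6.2 | 49.5 / 53.7 | 4.2 |
| 0.001 | 1.5 | 6.2 / 7.6 | 51.6 / 58.9 | 7.3 | 5.0 / 5.9 | 47.0 / 53.8 | 6.8 |
| 0.001 | 2.0 | 3.9 / 7.8 | 45.7 / 60.8 | 15.1 | 3.0 / 6.1 | 40.6 / 56.2 | 15.6 |
| 0.0003 | 1.0 | 7.4 / 8.0 | 78.4 / 79.0 | 0.6 | 6.0 / 6.1 | 74.0 / 75.2 | 1.2 |
| 0.0003 | 1.25 | 5.8 / 6.4 | 75.2 / 78.5 | 3.3 | 4.5 / 5.4 | 71.5 / 75.2 | 3.7 |
| 0.0003 | 1.5 | 5.6 / 8.6 | 74.0 / 81.0 | 7.0 | 4.4 / 6.6 | 70.0 / 77.4 | 7.4 |
| 0.0003 | 2.0 | 3.0 / 7.1 | 61.8 / 80.1 | 18.3 | 2.2 / 5.6 | 56.2 / 76.3 | 20.1 |

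**Reading the table.**

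- The mechanism shows in the model standard error of the log odds ratio. With ICC 0.001 and no treatment effect, it is 0.286 without county and 0.270 with it at a county odds ratio of 1.5 (ratio 1.06). At 2.0 it is 0.302 and 0.266 (ratio 1.14).
- Part of each power gap is a move in type I error. At ICC 0.001 and county odds ratio 1.5, the unadjusted z test (type I 6.2%) and the adjusted t test (5.9%) have nearly equal error rates, and their power is 51.6% and 53.8%. At near-equal error the gain is therefore about 2 points, not 7.
- With county included, z rejects at 7.6 to 8.2% at ICC 0.001 and t(20) at 5.8 to 6.2%. Moving from z to t costs 4.5 to 6.2 points of power at ICC 0.001 and 3.3 to 3.8 at 0.0003.

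**The case against.** The strongest reply is that the article defers detail to a later analysis plan, where a county term may well appear. That deserves weight, but the article does not leave covariates wholly open. It lists them for the other models without county, and it adds township and village random effects to match the sampling while leaving out the stratum of that sampling.

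It is also fair to say that the size is assumed. The article gives one average notification rate for the two counties together, 134/100,000, and no county-specific rate. If the counties are alike, the omission costs almost nothing. This stands, and every figure here is conditional on it.

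Three stronger readings are tempting and are not supported:

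- A reader might infer that the plan uses large-sample inference on 23 townships and so runs a 5% test at 7 to 8%. No section fixes a z or likelihood-ratio test, and that choice is ordinary content for the later plan. The direction is not fixed either: few clusters with z raise the error rate, while omitting a strong stratum lowers it (3.0 to 3.9% with z at a county odds ratio of 2.0).
- A reader might take the Discussion's statement, "We believe the randomization procedure will minimize any confounding effects from the baseline effect in the two groups", as a defect to be cured with pre-trial township notification rates as a covariate. The article does not show that such rates are available by township, it lists the missing baseline survey openly as a limitation, and extra covariates with 23 units are a trade-off.
- A reader might say that power is lost for free whatever happens. That fits only the county term, and only if the counties differ. The small-sample companion has its own cost.

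**Conclusion.** The point holds in a limited form. The design stratifies by county, and the primary model as stated does not carry that stratum. The consequence is loss of efficiency, not bias: wider intervals and a more conservative test than the same model with county.

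On the z reference the loss in power is about 1 to 3 points with no county difference, about 7 at a county odds ratio of 1.5, and about 15 to 18 at 2.0. The t reference gives similar gaps, up to 20 at 2.0 with the smaller ICC. Part of each gap, and at 1.5 a large part, is the change in type I error. These sizes rest on assumed county ratios, an assumed split of townships by county and an assumed township-level ICC. The direction does not depend on the particular values once the counties differ.

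The reference distribution is unstated, not wrong. It matters here because adding county while keeping z would leave the error rate near 8%.

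**What to change.** State in the analysis section, or in the forthcoming analysis plan before outcome data are examined, that county is a fixed effect in the primary beta-binomial model. Do the same for the secondary rate-based, patient-level and continuous models. In the fallback with township as a fixed effect, county is already absorbed by the township terms. Keep the county subgroup analysis as a separate question about effect modification.

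In the same sentence, name the reference for the primary test and interval: t with 20 df (23 townships less 3 mean parameters: intercept, allocation, county), or a permutation test that reshuffles allocation within county.

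The county term costs one degree of freedom and needs no new data. The t reference costs about 4 to 6 points of power against z at ICC 0.001 and brings the error rate to about 6%, close to nominal but not exactly 5%; this is a reason to report the permutation p-value beside it.

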### Eligibility criteria

#### Clusters.

Township is treated as the cluster of intervention. A township is an administrative unit with a township hospital and consists of 7–12 villages. All townships in Xincheng and Xiangzhou county, which provide their willingness to participate, will be included. Villages within the participating township serve as sampling units in the epidemiological survey at Year 3 to determine the TB prevalence rate.

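### The non-convergence fallback makes township a fixed effect, which is collinear with township-level allocation, so these secondary models could not estimate the main intervention effect

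*Protocol article*

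**What the plan says.** Allocation is by township. Under Clusters, the protocol says "Township is treated as the cluster of intervention". Under Recruitment, randomization and blinding, the statistician will "randomize all recruited townships, stratified by county", "assigning them to the control and intervention group in an overall 1:1 ratio (12 intervention vs 11 control"). The reason given is "We will implement the ACF activities at the township level to avoid contamination among villages".

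The Statistical analysis section then sets out three kinds of model:

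- **Primary and rate-based secondary outcomes:** "For the primary outcome and all secondary rate-based outcomes (aggregated to the township level), the statistical analysis will employ a beta-binomial regression model". No fallback is attached to this model. The section treats the cluster-level estimates as the main evidence on effectiveness.
- **Secondary patient-level analysis:** adjusted for age, sex and ethnicity, "using a mixed-effects logistic regression model including random effects for township and village (to reflect the sampling strategy").
- **Continuous outcomes:** "For continuous secondary outcomes we will employ a linear mixed-effect model with random effects for township and village", with the same three adjustment variables.

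For the second and third kinds, if the two-level model does not converge, "models where township is included as a fixed effect rather than random will be employed". The rule appears once in each of the two paragraphs. In the continuous-outcome paragraph, the sentence that follows it still promises a covariate-adjusted difference in means between arms with its 95% interval.

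**The concern.** In a cluster-randomised trial, the information about the intervention lies between clusters. Everyone in a township has the same arm, so there is no within-township comparison of intervention with control. A fixed effect for each township absorbs all between-township differences, and the arm difference goes with them. The fallback would therefore remove the quantity it is meant to rescue.

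At stake is the covariate-adjusted estimate for the rate outcomes, because the patient-level model is the only stated analysis of them that adjusts for age, sex and ethnicity. There are two ways it could go wrong. The software may return no arm estimate. Or it may drop an extra township indicator and print a number under the arm label that is not an intervention effect. Either would leave a replacement model to be chosen after outcome data are in hand.

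**Working it through.** **Inputs.** 12 intervention and 11 control townships (Recruitment, randomization and blinding). Prevalence 300 and 150 per 100,000, ICC 0.001, 500 participants per village, 47 villages or 23,500 participants per group (Sample size).

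**1. The plan's own figure.** The pooled two-sided comparison of 0.0030 with 0.0015 at 5% and 80% power needs 15,662 per arm. The village design effect is 1 + (500 − 1) × 0.001 = 1.499. Then 15,662 × 1.499 = 23,477, and 23,477 / 500 = 46.95, so 47 villages. The stated sample size reproduces. It does not bear on identifiability; it only supplies the case counts in step 5.

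**2. Rank.** Let D1 to D23 be the township indicators, with townships 1 to 12 in the intervention arm. Then arm = D1 + D2 + … + D12 exactly. The 23 indicators plus arm give 24 columns of rank 23.

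With an intercept, 22 township indicators, age, sex, ethnicity and arm (covariates simulated; 47 + 47 villages), there are 27 columns of rank 26. Without arm there are 26 columns, also of rank 26. Regressing arm on the other columns leaves a residual sum of squares of about 2 × 10⁻²⁶, which is zero to machine precision. Individual covariates do not help. Nor does a village random effect, which leaves the fixed-effect columns unchanged.

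**3. What software might print.** One simulated continuous data set with a true arm effect of 0.5 was refitted four times, changing only which township was omitted from each arm. The arm coefficient was −0.06, 0.83, 2.61 and 2.39. The residual sum of squares was 1869.35 each time. The fits are identical, so the coefficient reflects only the choice of reference townships.

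**4. What stays estimable.**

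| Fixed part of the model | Columns | Rank |
|---|---|---|
| Township random: intercept, arm, age, sex, ethnicity | 5 | 5 |
| The same plus county (illustrative assignment) | 6 | 6 |
| Township fixed, arm-by-sex interaction, no arm main effect | 27 | 27 |

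The interaction varies within township and survives. The arm effect for men or for women separately does not.

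**5. Case counts and precision.** Expected survey cases are 23,500 × 0.0030 = 70.5 (control) and 23,500 × 0.0015 = 35.25 (intervention). The total is 105.75 over 94 villages, about 1.1 per village. Programme-reported cases are added to the numerator, but the protocol does not say how many.

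Approximate standard errors of the log odds ratio, with cases spread evenly over townships:

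- One intervention township (35.25 / 12 = 2.9 cases) against one control township (70.5 / 11 = 6.4): √(1/2.9 + 1/6.4) ≈ 0.70.
- All townships, no clustering: √(1/35.25 + 1/70.5) ≈ 0.21.
- All townships with a township design effect: 47,000 / 23 ≈ 2,043 per township, so 1 + 2,042 × 0.001 ≈ 3.04, and 0.206 × √3.04 ≈ 0.36. This assumes that the ICC of 0.001 applies at township level.

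**The case against.** The strongest reply concerns reach, and most of it stands. The primary outcome and all rate-based secondary outcomes have a township-level model without this rule. The patient-level analysis is secondary and is only to be attempted. The numbered secondary outcomes are one prevalence rate and two notification rates, so the linear model has no listed target; costs have their own section. The fault bites only if a model fails to converge.

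Three stronger readings are tempting, and the documents do not support them.

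- **A reader might infer that convergence failure is likely.** About 1.1 survey cases per village is sparse for two variance components, and the protocol itself foresees failure. But no failure rate has been shown, sparse data often give a zero-variance fit rather than non-convergence, and programme-reported cases will raise the count.
- **A reader might infer a deceptively narrow interval.** An arbitrary two-township contrast omits between-township variance, yet its standard error of about 0.70 exceeds the 0.21 to 0.36 of the intended comparison. The harm is an arbitrary or absent estimate.
- **A reader might infer that the planned sex subgroup analysis becomes wholly undefined.** The interaction remains estimable; only the sex-specific intervention effects are lost. The protocol also makes this subgroup conditional on the patient-level analysis succeeding.

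Two defences do not stand. The promised later analysis plan does not excuse the rule, because this is not an omitted detail: the protocol fixes it, twice. Nor does it help that an analyst could make arm estimable by adding a constraint on the township effects. The protocol states none, and the answer would depend on the one chosen.

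**Conclusion.** The point holds with limited reach. As written, the fallback cannot deliver a main intervention effect in either model to which it is attached (24 columns, rank 23). In the continuous-outcome paragraph it contradicts the estimate promised in the next sentence. This rests only on whole-township allocation and on reading the fallback literally, with one effect per township; it does not depend on prevalence, ICC or sample size.

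The damage is confined to the secondary patient-level logistic model and to any continuous outcome that may be analysed. A reader might infer that the trial's main conclusion is exposed. It is not: the primary beta-binomial analysis is unaffected. The rule should be fixed before the analysis is run, but it is not a threat to the primary result.

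**What to change.** Replace both fallback sentences with a rule that keeps arm estimable. One workable sequence is:

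1. On non-convergence, drop the village random effect and keep the township random intercept.
2. If that also fails, use generalised estimating equations, or regression with township-clustered standard errors, with a small-sample correction for 23 clusters. A covariate-adjusted two-stage analysis of township summaries is an alternative.

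Add that township will not be a fixed effect in any model estimating the intervention effect. County, the stratification factor, may be a fixed effect, since arm varies within county. The order of these steps is a matter of preference; the requirement is that arm remains estimable and township clustering is respected.

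The cost is two sentences in the protocol, carried into the analysis plan. No new data are needed, and the sample size and primary analysis do not change.
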